## **VII. Study Implementation and logistics**

### **A. Clinical Center Organizational Structure and Infrastructure**

Each Clinical Center has a set organization structure with clearly defined personnel roles, a well-maintained computer infrastructure, and plans to establish numerous mechanisms to promote the flow of information between study center sites and the DCC.

[name] and colleagues at the Washington University in St. Louis, MO has been designated as the lead Clinical Center for this grant. [name] at Boston University Medical Center and [name] at Kaiser Permanente and University of California at San Diego are the PIs of their respective Clinical Centers. [name] will schedule and lead regular conference calls to discuss the processes of recruiting, adherence, and retention throughout the trial, and will report directly to [name] at the DCC.

Because recruitment of participants will take place in Obstetrics Clinics, it will be crucial for each Clinical Center to establish ties and obtain cooperation from their respective Obstetric practices. All three centers have working relationships with the Obstetric practices from prior recruitment efforts. In the St. Louis Center, [name] will support the trial by setting into place the system to recruit the pregnant women and obtain the necessary samples of peripheral blood during the prenatal visits and peripheral and cord blood at the time of delivery as well as obtaining urine to be measured for creatinine and calcium as safety for vitamin administration during pregnancy. [name] will assure that the OB practitioners are familiar with the trial and will support enrollment of their patients into the trial. [name], MD, PhD (Chair, Dept. of OB and Gyn) and [name], CNM (OB Department Manager), will fulfill the same roles for the BUMC and Kaiser Permanente San Diego Clinical Centers, respectively.

In each Center, a Study Coordinator will be responsible for recruiting pregnant women into the trial at the time of their first visit to the OB offices and retaining them during the 4 years of their involvement in the trial. Specific activities of this Study Coordinator will include but not be limited to:

- Working with the clerical staff of the OB department to assure that a brochure describing the vitamin D trial is included in the materials sent to the pregnant women giving information about the first OB visit.
- Working with the staff at the OB offices to determine when eligible women will have their first OB visit and being in the clinic to meet the women to give them information about the study, determine their level of interest, perform appropriate screening, give the informed consent and arrange a time for discussion of the trial and the consent and answer any questions.

- Make an appointment in the Study Clinic for enrollment and initiation of the study medication. The trial will also provide standardized prenatal vitamins, which will be initiated at this visit.
- Remain in contact with the participants via scheduled phone calls and as needed for problem solving about taking study medication and the prenatal vitamin.
- Work with the staff in labor and delivery to establish a system for collection of peripheral blood from the mother to be used for assay of vitamin D and the cord blood for assay of vitamin D and for use in extraction of DNA to be used in the genetic studies.
- Visit the now new mother and her baby after delivery to deliver a small gift and further develop the relationship that will assure long-term follow-up of the child with the quarterly phone calls and annual visits.

Each Center will also have a second Study Coordinator or Study Nurse who will be a partner of the other research patient coordinator in performing all the duties listed to assure recruitment and retention of the women and their offspring.

## **B. DCC Organizational Structure and Infrastructure**

The DCC has a set organization structure with clearly defined personnel roles, a well-maintained computer infrastructure, and plans to establish numerous mechanisms to promote the flow of information between study center sites and the DCC.

The DCC will be chaired by [name] and [name], and the statistical and informatics component will be managed by [name]. The DCC informatics operations will be executed by [name] staff, which has an outstanding track record running multicenter trials funded by AHRQ and NHLBI since the mid 1990s. [name] will be the Senior Data Manager for the trial, along with, Deputy Data Manager, [name], Senior Programmer, and [name], Administrator. In consultation with [name], [name] will specify the general communications and data archive workflows for the support and programming staff members. As the design of forms and general data flow processes evolves, prototypes and "dry run" exercises will be carried out with the clinical sites to verify the soundness and feasibility of the operations plan. The detailed task sets will be noted in the DCC Manual of Operations, which will be available through the internal study web site. The DCC will have full staff meetings attended by one of the PIs every month, and basic staff meetings every week. In addition, the chairs of the DCC will have a conference call with the PIs of the Clinical Centers once a month to obtain updates on recruitment and progress of the trial, and discuss any issues that pertain to the conduct of the trial.

## **C. Randomization and Treatment Assignment**

Participants who consent and are deemed eligible to participate will be randomized by the Data Coordinating Center (DCC) to either of the 2 arms of the trial and will be sequentially assigned a six-digit Study Identification Number (Study ID). The first digit of the Study ID will identify the site (St. Louis, San Diego, or Boston) and the next four digits will identify the participant; and the last digit will be a check digit that is calculated from a formula to ensure the accuracy of data entry. Only those who indicate their intention to follow-up until the child is 3 years old will be randomized. Randomization will be performed prior to enrollment of any study participants by the DCC using a system that automates the random assignment of treatment groups to Study ID numbers. The randomization scheme will employ permuted blocks, and one blocked allocation list per stratum (study site and racial/ethnic group) will be generated. That is, separate permuted block randomization lists will be maintained for each racial/ethnic group – White/Non-Hispanics, White/Hispanic, Black (including Hispanic Black), and Other – within each study site. This will ensure that within each site, there is approximate balance across arms over the course of enrollment, and that within ethnic groups within site, there is also approximately

equal representation on both arms. A woman who is deemed eligible will receive the next available Study ID number for her given study center site and ethnic group. The Study ID will be linked to the women's Screening ID. It should be noted that women who are deemed ineligible will not receive Study IDs (i.e. randomization to a treatment). This will help ensure balance in treatment and control groups by not 'wasting' randomization assignments on ineligible subjects.

**C.1. Race and Ethnicity.** Race and ethnicity will be collected according to NIH categories. Participants will be asked to first categorize their ethnicity as either Hispanic or not Hispanic. They will then be asked to categorize their race as either White, Black or African-American, Asian, Native Hawaiian or other Pacific Islander, American Indian/Alaskan Native, or Other. If the participant categorizes herself as Black or African-American, she will be considered Black for purposes of randomization regardless of any other ethnic or racial category she has picked. If the participant categorizes herself as non-Hispanic and White, she will be classified as White/non-Hispanic. If she picks Hispanic but not Black, she will be classified as White/Hispanic. Any other racial or ethnic combinations will be classified as Other.

#### **D. Trial Website**

Each Center's participants will have access to the trial website. The DCC will establish a website with both public and private (SSL regulated, LDAP database of all study investigators or support staff needing website access will be established with private passwords) web portals at the beginning of the recruitment period. The public pages will provide information on the scope and background of study to assist in recruitment. The private pages will allow for general posting of any protocols changes or announcements, current versions of forms, minutes of phone calls, manuscripts in development, allow investigators to monitor recruitment process, and provide other general information. Patient-level treatment information, medical history, or endpoint information will not be linked to the website. The website will be maintained throughout the trial and closeout period, and aggregate study findings will be posted at the end of the trial.

#### **E. Data management and tracking**

Clinical data from screening (first prenatal visit), each subsequent pre-natal visit, delivery day, quarterly follow-up questionnaires, and clinic assessment visits at 1, 2, and 3 years are entered on forms at each study center at the time of the patient visit/contact. The forms will be reviewed by the center coordinator, and uploaded to the internal study website.

Calcium/creatinine ratios will be conducted by the study center laboratory on the day of the patient visit. The calcium/creatinine ratios will be reviewed by the laboratory head at each center. Alert values will be established and if reached will lead to immediate contact to the Study Coordinator and contact with the participant will be attempted within 24 hours of identification. Blood draws for 25(OH)D levels will be sent from the study center laboratory to the DCC on a weekly basis, where they will be logged in and aliquots created for 25(OH)D assays.

Upon receipt on collected forms, all data forms (lab work and patient questionnaires, clinical assessments, etc.) will be downloaded from the internal website and double entered at the DCC with range, logic, and missing data checks built into the data entry software application. The data entry software will be configured to be schema-driven, so that an abstract schematic design is at the base, and the concrete (XML) schema that specifies form content and logic is automatically transformed to a functional data entry application. We currently use Altova XMLSpy and Microsoft InfoPath technologies to implement the schema-driven design. Forms with missing (illegible entries will be considered missing for the purposes of data entry) and/or inaccurate (i.e. out-of-range) entries will not be accepted into the system database, but will be cycled back to the site for correction.

For clinical data, the data monitor will send weekly reports of missing or inappropriate entries to the study project coordinators for clarification and resolution. Additionally, cross-form edit checks will be performed on a monthly basis, to detect unresolved problems. Data inconsistencies occurring across forms will be resolved with the assistance of study center staff. Standardized edit reports that summarize problems in the database provide an additional method of assuring data quality. To ensure accuracy of patient identification numbers (in particular, minimizing transposition error), digit checks will be utilized. Digit checks will identify whether there are inconsistencies in patient identification numbers across collection time points. Once data have been verified, data will be archived on a monthly basis as a SAS dataset. Data will be stored in coded form (i.e. numeric coding for ethnicity or gender) using standard codebooks currently implemented

For each patient, a data collection tracking query will be developed, which will contain expected time points for each data form/lab work, based upon patient's initial enrollment date. Forms more than one week late (from enrollment to delivery) or one month late (after delivery to year 3) will be flagged as missing, and a query will be generated for each site that contains a list of patient IDs and their outstanding forms/lab data. The data manager at the DCC will follow-up with site coordinators to track down any missing forms. For patients at-risk of dropping out (i.e. missed appointment or non-response to questionnaire request), the study coordinator or research assistant will make repeated attempts to contact the patient. A subject will be dropped only with explicit withdrawal request by the pregnant woman (initially) and later, the parent of the infant/child. Even with missed appointments or calls, every effort will be made to complete the final in-person visit when the child is 3 yrs old.

## **F. Data Security and Confidentiality**

All computer files are stored in password-controlled accounts on DCC computers. There will be an SSL regulated private web portal established for the study at the DCC, LDAP database of all study investigators or support staff will be established with private passwords allocated to all who have a need to examine the study web site

Each participant will be assigned a unique study identification number. Once these data are linked (after a subject successfully enters randomization phase from screening), the study identification number will be the primary identification number. The data coordinating center and trial statisticians will have access to only the unique identification number and therefore cannot link names to data. Files of study data will include the screening and study identification number but not participant names. Any hardcopy of data forms obtained by the coordinating unit (for example, as part of spot-checking for quality control) will be maintained in locked file cabinets. If a participant withdraws from participation at any point in the trial, and requests withdrawal of any information from the database, the clinical center staff will forward the study identification number to the DCC and all files pertaining to that identification number will be removed and destroyed.

At the clinical centers, data are collected on forms with fields for study identification number but without a field for the participant's name. Still, separate lists of participant names, identification numbers, and contact information are used during the study to maintain contact with participants and eventually to provide feedback on study and personal results. These lists will only be available to Center Co-PIs and staff with direct patient contact. All hardcopies of forms are stored in locked file cabinets. All computer files are password protected. Participant results will only be released to the participant unless he/she provides written approval to release data (e.g. laboratory results to personal provider). Data will only be presented and published in aggregate, i.e. no identifying characteristics of participants will be published or presented.

## **G. QC protocol**

To ensure uniform data collection and reporting procedures, training and certification of study center research assistants (RAs) will occur at the DCC. Additionally, there will be a weekly conference call between the DCC deputy data manager and the site coordinators at each center to globally address any screening or data collection issues and maintain study-wide consistency in procedures. Monthly conference calls will be conducted between the DCC PI and all site investigators to check progress and data integrity. Patient recruitment and follow-up, as well as data collection and archiving procedures, will be monitored by the DCC with bi-annual site visits. 20% of the patient questionnaires and lab forms will be randomly sampled and queried against stored values in the DCC database and archives.

To verify the accuracy of 25(OH)D measurements obtained by the Channing Laboratory, 20% of the maternal blood samples, as well as cord blood samples at delivery, will also be sent to [name] lab. Any discrepant lab values will be checked to determine the source of the variation. If appropriate, a replicate assay will be conducted. Samples will also be obtained from each lot of the vitamin D supplement (4000 IU vitamin D) and prenatal vitamins (400 IU vitamin D) and sent to the lab of [name] for analysis to ensure the level of Vitamin D compound in each is within the range specified in trial protocol.

The DCC will provide monthly reports on the timeliness, quality and completeness of the data to the Steering Committee, organized by type of visit, e.g. screening visit 1, randomization day, 6-month visit, etc, and by specific data form. The Steering Committee will remain informed of any potential screening or data collection issues (with patient forms or lab work) and be able to recommend protocol changes or study center intervention as necessary to resolve any outstanding concerns.

## **H. Blinding**

Until the end of the trial, all investigators, clinical staff and participants are masked to trial outcome data, with the exception of the trial statisticians, and the data manager. Due to the nature of the intervention, laboratory technicians and staff obtaining calcium/creatinine ratios may be able to infer treatment group assignment. However, there are other more common causes of elevated calcium/creatinine ratios (i.e. dehydration). Therefore, we do not anticipate any issues with unintentional unblinding of study investigators or clinical staff. There may be a rare case where emergency unblinding may be necessary (e.g. overdose of study pills or persistent elevation of urinary Ca/Cr ratio with hypercalcemia and hypervitaminosis D). In this case, emergency unblinding will occur at the discretion of the DCC and appropriate actions will be taken, including immediate reporting to the DSMB. In cases where non-emergent unblinding may be necessary, The DCC PIs will seek input from the DSMB prior to unblinding.

For quality control purposes, 20% of the blood samples will also be sent to [name] lab for 25 (OH) D measurements. However, we will adhere to established procedures to maintain separation between laboratory staff and clinical staff that have patient contact. For quality assurance, [name] will receive a report of measured 25(OH)D levels that are stripped of all identifying patient information (identifier and clinical information).

To ensure rapid intervention in the unexpected event of out-of-range ( $\geq 1.55$  mmol/mmol) calcium/creatinine ratios, urinary calcium and creatinine measurement will be conducted at each Clinical Center's Clinical Chemistry Laboratory. Again, we will adhere to established procedures to maintain separation between laboratory staff and clinical staff that have patient contact or are responsible for measuring primary or secondary endpoint outcomes. In the event of an out-of-range calcium/creatinine ratio, the patient will be contacted for follow-up, with the procedure detailed in Section I below.

Given the benign treatment intervention, the manufacturing of prenatal vitamins, placebo and Vitamin D supplement by the same drug company (Tishcon Corp), the distribution of study vitamins by the DCC, off-site assays of 25(OH)D levels, protocols to maintain separation

between information available to laboratory staff, trial statisticians, the DCC, and site clinical staff and investigators, we anticipate that we will successfully maintain blinding of all investigators, clinical staff and participants to both treatment intervention and trial outcome until the end of the trial.

### **I. Data Safety and Monitoring of Each Subject**

An external Data Safety and Monitoring Board (DSMB), composed of vitamin D metabolism experts, early life asthma experts, obstetricians, an ethicist, and a statistician has been appointed by the NHLBI. The board will be convened prior to study initiation to review the protocol and to examine and comment upon "shell" reports that will be used to illustrate data accumulation as the study proceeds.

All study subjects will be monitored for hypervitaminosis D, the only known toxicity of which is hypercalcemia. Operationally, we will define caution by urinary calcium/creatinine ratio  $\geq 1.55$  mmol/mmol from the samples that are obtained monthly starting 1 month after randomization. Whenever any patient exceeds the caution limit, the study medication will be temporarily discontinued and a specific case study will be initiated. The first elevated urine Ca:Cr ratio will trigger the repeat measure of the urine calcium/creatinine ratio after hydration (drinking at least 8 oz of water prior to coming in for the visit). If the repeat urinary calcium/creatinine after hydration remains elevated, the patient will have serum calcium and vitamin D levels checked at the Clinical Center's Clinical Chemistry Laboratory. If the serum calcium and vitamin D levels are within normal limits, the subject will resume study medication. Predefined cutoff of a calcium of  $\geq 10.2$  mg/dl or vitamin D level of  $\geq 300$  nmol/L are criteria for removal from the study treatment. The subject will still be followed in the intention-to-treat paradigm. Further evaluation (including the possibility of taking additional calcium or vitamin D supplements as well as workup for other disorders such as hyperparathyroidism) will be pursued further depending on the serum calcium and vitamin D levels as appropriate. The appropriate IRB will be notified, and the NIH and FDA will be notified per their protocols. The DSMB chair will be notified, as with any severe adverse event. After the detailed case review has been performed by the clinical center to ascertain the cause of the hypervitaminosis D in the subject and reviewed by the DSMB to make an informed decision about the study's continuation. If the elevated levels in the subject are attributed to the vitamin D supplement, the subject will be withdrawn from supplementation but will continue to be monitored.

Subjects who have a subsequent elevated urine Ca:Cr that is a lower ratio than the initial measurement will remain on the study medication and no further action will be required. If the ratio of any subsequent spot urine is greater than the initial ratio, the woman will be asked to stop study medication, and be reminded to properly hydrate. She will be asked to return to the clinical center where blood will be drawn to determine serum Ca and 25(OH)D levels, no repeat urine is required at this time. If the levels of both are within the normal range, the subject will resume study medication and continue to be monitored per protocol each month (with any other elevated ratio again being compared to the initial elevated ratio). If either of the serum values are outside of the normal range, the procedure outlined above will be followed.

### **J. Adverse Events and Reporting to the DSMB**

- Serious Adverse Events (SAEs) will include the following:
  - Symptomatic hypercalcemia and/or elevated 25(OH)D level (as defined above)
  - Pre-eclampsia and Eclampsia
  - Any hospitalization of mother (including severe pregnancy complications such as HELLP [Hemolytic anemia, Elevated Liver enzymes, Low Platelet count] syndrome, deep vein thrombosis or coagulopathy), except for
    - Delivery after 32 weeks

- Pre-term labor not resulting in delivery
- Any newly diagnosed serious maternal illness
- Maternal death from any cause
- Pre-term delivery <32 weeks gestation
- Discovery of major fetal anomalies or diagnosed major congenital anomalies (note: an elective abortion in the absence of diagnosed congenital anomalies will be considered a study withdrawal, not an SAE)
- Still birth/Intrauterine fetal death
- Neonatal demise
- Any neonatal intensive care admission
- Adverse Events (AEs) will include (but not limited to):
  - Pre term delivery between 32 and 37 weeks
  - Gestational diabetes
  - Gestational hypertension
  - Perinatal infections
  - Anemia
  - Prolonged rupture of the membranes
  - Placental abnormalities such as previa or marginal abruption
  - Meconium staining
  - Abnormal labor
  - Low birth weight (<1500g)
  - Asymptomatic hypercalcemia ( $\geq 10.2$ mg/dl)
  - Hypercalciuria
    - Urine calcium/creatinine ratio  $\geq 1$  after repeat measure. If ratio normalizes after hydration this is NOT an adverse event

The occurrence of adverse events (AE) and serious adverse events (SAE) will be monitored by each Clinical Center through the monthly maternal health questionnaire and the monthly OB medical record review. Additionally, hypercalciuria will be monitored with the monthly urinary calcium excretion. Monitoring of these urine samples are detailed above. If a SAE is discovered, the Clinical Center staff, under the direction of the Clinical Center PI, will fill out the SAE form and determine whether this event was likely to have been related to the study medication. The form will then be uploaded to the secure VDAART website and an email will be automatically generated to alert the DCC co-PIs and staff. The DCC staff will then review the form for any errors, missing or incomplete information, or any inconsistencies. The form will then be uploaded within to the secure DSMB page on the website after approval by one of the DCC medical staff members ([name] or [name]). The DCC is expected to complete this review and approval, and upload of the SAE form to the DSMB page of the secure website within 72 hours of being notified by the Clinical Center. Once the SAE form has been uploaded, an email from [name] and [name] will be generated notifying the DSMB Chair and the NHLBI staff. The DSMB Chair will then review the form and involve other DSMB members as he deems appropriate. The DSMB Chair will then communicate with the DCC Staff by email regarding the outcome of the review, including instructions for the DCC to report the SAE to the FDA and the Clinical Center IRBs, if found to be likely related to the study medication. Otherwise, the DCC will prepare annual reports of all SAEs and AEs to the FDA and the IRB at each center.

AEs will also be monitored via the above mechanism. Once an AE is identified, the appropriate form will be completed. These forms will be uploaded to the secure VDAART website as soon as they are completed. The DCC staff will review these forms and prepare quarterly reports to the DSMB. These quarterly reports will be uploaded to the DSMB page of the secure website and an email will be generated notifying all DSMB members and NHLBI staff. All adverse events

will be reviewed by the entire DSMB at quarterly intervals, by e-mail, in between the regularly scheduled semi-annual meetings. SAEs and AEs will be reported by masked treatment groups. In addition, all SAEs and AEs will be reported by ethnicity and gender (for events among the infants), and with information about the expected rate of occurrence of these events in a general population of pregnant women (or infants). The Director of NHLBI, with advice from the DCC and the DSMB, will have the sole power to stop the study in the event of an unanticipated statistically and clinically significant difference between arms in rates of serious adverse events, whether or not these are attributable to the study treatment. The definition of statistical significance for study stopping will be adjusted  $\alpha = 0.01$ .

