#### IV. Study Overview and Subject Selection

This is a multicenter, randomized, double-blind, controlled clinical trial that compares high-dose vitamin D3 supplementation (4,400 IU/day) vs. usual dose vitamin D3 supplementation (400 IU/day) in pregnancy to prevent asthma in the women's children. The study base will be all pregnant women from each Clinical Center who have a personal history of asthma and/or allergies or a history of asthma and/or allergies in the biologic father of the child (i.e. a "high risk" cohort for asthma and allergies in the child). Eight hundred seventy women (435 in each arm) will be followed through their pregnancy and delivery, and their infants will be followed up to the age of 3 yrs. All infants who are consuming < 1000 ml of formula per day will be offered vitamin D supplementation (400 IU/day) in accordance with the most recent recommendations from the American Academy of Pediatrics. This includes all infants who are breastfed, either partially or exclusively, and all formula-fed infants until they consume at least 1000 ml of formula. The primary outcomes are doctor-diagnosis of asthma and recurrent wheezing at age 3 yrs. Due to dropouts from miscarriages, stillbirths, other pregnancy complications, and loss-to-follow-up, we expect that we will be left with 660 3-yr old children (330 in each arm) for the analyses of the primary outcome (see Specific Aims in Section II above).

Women who come into their Obstetrician's clinics for their first pre-natal visit will be screened on a daily basis by a Study Coordinator and a physician co-investigator will verify eligibility criteria.

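### Section VII.J lists no child death or hospital admission after the neonatal period and names no source that would find one, although the children are followed to age 3

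*Supplement*

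**What the plan says.** All references are to the current protocol unless stated otherwise.

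- **Serious events.** VII.J introduces the list with "Serious Adverse Events (SAEs) will include the following". For the mother it includes "Any hospitalization of mother" (with stated exceptions) and death from any cause. For the fetus or child it has delivery before 32 weeks, major anomalies, stillbirth or intrauterine death, "Neonatal demise" and "Any neonatal intensive care admission".
- **Other events.** The second list is open: "Adverse Events (AEs) will include (but not limited to". Every item that it names is maternal, obstetric or perinatal.
- **How events are found.** Adverse and serious adverse events "will be monitored by each Clinical Center through the monthly maternal health questionnaire and the monthly OB medical record review", with monthly urine calcium in addition. For the non-serious events, "AEs will also be monitored via the above mechanism".
- **Child follow-up.** Section IV says of the women that "their infants will be followed up to the age of 3 yrs". VI.M describes a questionnaire every three months on the child's general and respiratory health, and Table 2 adds visits at years 1, 2 and 3.
- **Use of the events.** VII.J reports serious and other events by masked treatment group. It lets the trial be stopped for a between-arm difference in serious event rates at an adjusted alpha of 0.01, whether or not the events are attributable to treatment.

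The Addendum to the Analysis Plan defines efficacy outcomes and adds nothing on safety events in the child.

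**The concern.** The intervention is given in pregnancy, and its effect is read in the child at age 3. The efficacy comparison therefore uses the whole of childhood follow-up, while the listed child deaths and admissions end with the neonatal period. For the mother, the list takes in death from any cause and most hospital admissions. For the child, it has no equivalent after the newborn weeks.

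At stake is the arm-level safety evidence in the children. The safety reports and the stopping provision in VII.J, and the safety grounds for termination in VII.K, all work on reported adverse events. If later child events are neither listed nor looked for, the monitoring board's tables may show nothing on them by arm, and an empty table could be taken as reassurance. The timing also matters, because the oldest children are well past the neonatal period while other women are still being enrolled and treated.

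**Working it through.** **1. Do the lists and the sources reach the child after the neonatal period?** This is a reading of the text, so the relevant places are set side by side.

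| Element | Where | Reaches the child after the neonatal period? |
|---|---|---|
| Death items | VII.J, serious list | No: fetal death/stillbirth and neonatal death only |
| Admission items | VII.J, serious list | No: mother, and neonatal intensive care |
| Anomaly item | VII.J, serious list | Listed with no time limit |
| Non-serious list | VII.J | Open wording, but no such item is named |
| Monthly maternal questionnaire | VI.D, Table 2 | No: given at prenatal visits |
| Monthly record review | VI.E, Table 2 | No: obstetric record, for complications of pregnancy |
| Urine calcium | VI.G, Table 2 | No: the mother, during pregnancy |
| Infant questionnaire, yearly visits | VI.M, Table 2 | Yes, but VII.J does not name them as event sources |

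The open non-serious list would admit a later child event in principle, but none of its named sources would find one. The same holds for an anomaly diagnosed late.

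**2. The plan's own denominator.** Q.1 gives 870 women, 8% pregnancy loss, 17-18% loss to follow-up, and 660 children.

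- Births: 870 × (1 − 0.08) = 800.4.
- At age 3: 800.4 × 0.83 = 664; × 0.825 = 660; × 0.82 = 656.

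The stated 660 is reproduced.

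**3. Share of child follow-up outside the listed death and admission items.** Two assumptions are needed. The neonatal period is taken as 28 days, since the documents do not define it. Loss is taken as linear from 800 to 660 over three years.

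- Total child-years: 3 × (800.4 + 660) / 2 = 2,190.6.
- Neonatal child-years: 800.4 × 28 / 365.25 = 61.4.
- Outside: 2,190.6 − 61.4 = 2,129.2, and 2,129.2 / 2,190.6 = 97.2%.
- For a child followed for the full three years: 1 − 28 / 1,095.75 = 97.4%.

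**4. What might fall there.** The documents give no child death or admission rates, so these are illustrations on assumed rates.

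- Post-neonatal deaths at 1-3 per 1,000 births: 800.4 × 0.001 to 800.4 × 0.003 = 0.8 to 2.4.
- Admissions at 3-8 per 100 child-years: 2,129 × 0.03 to 2,129 × 0.08 = about 64 to 170.
- Power to detect a doubling in the proportion of children admitted, two-sided alpha 0.01, 330 to 400 children per arm: 0.45-0.54 from an assumed 5% control proportion, 0.85-0.92 from 10%, and above 0.99 from 20%.

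Deaths could only be counted and described. Admissions might be numerous enough to compare.

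**5. Timing.** VII.L places the first deliveries at year 1 month 12, the last randomization at year 2 month 11 and the last deliveries at year 3 month 6. The oldest children would be about 11 months old when the last women are randomized and about 18 months old when the last women deliver. Later child events could reach the board while women are still being treated.

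**The case against.** The strongest case is that the scope was a considered choice. Study treatment is antenatal, and VII.I names hypercalcemia as the only known toxicity of hypervitaminosis D. The Summary of Protocol Changes shows that the event lists and the reporting process were revised on the monitoring board's recommendation. Asthma, wheeze, eczema and lower respiratory infection are compared by arm as outcomes, so serious respiratory illness is partly visible. Deaths would be too few to test.

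Much of this is true, but it does not close the gap. The stopping provision disregards attribution, so the end of treatment at delivery is no reason to leave later events out. Respiratory illness reaches the arms as efficacy data only, and neither deaths nor all-cause admissions follow from it. A small number of deaths argues against a formal test but not against counting them.

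The objection does rule out several stronger readings that a reader might infer:

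- *That a later child event can never enter the arm comparison.* The non-serious list is open, VII.J mentions events among infants, and staff could learn of an event at a quarterly call. The text supports only that no provision is made.
- *That a child death would be recorded as loss to follow-up and treated as missing completely at random.* No section classifies a death this way. VII.E drops a subject only on explicit request. P.2 checks for differential loss. Q.6 predicts that missingness is completely at random but also plans to test this and offers imputation. The documents are simply silent on child deaths.
- *That treatment is said to act years after birth.* P.2.a and VII.K place the action in utero; only the outcome is read at age 3.
- *That the trial undertakes to show child safety to age 3.* This is not among the five aims.

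**Conclusion.** The point holds as a gap in scope and ascertainment, and it should be mended. As written, VII.J gives no item for a child's death or hospital admission after the neonatal period, and none of its named sources would find such an event. About 97% of child follow-up time lies outside the listed child death and admission items. That figure rests on a 28-day neonatal period and linear loss; the finding about the text needs neither. The event counts and power figures rest on assumed rates and show scale only. The documents do not support saying that these events are certain to be missed, or that deaths would be miscounted.

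**What to change.** 1. In the serious event list of VII.J, add death of the child from any cause up to the 3-year visit.
2. In the ascertainment text of VII.J, name the quarterly infant questionnaires and the yearly visits as sources for serious and other adverse events. Adding the list item alone would not be enough, because the present sources stop with the pregnancy.
3. Add one hospital-admission item to the quarterly form if it is not already asked; VI.M does not say that it is. Tabulate admissions by masked arm in the regular reports, without expedited forms.
4. Report child deaths separately from loss to follow-up.

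The contacts already exist, so the cost is a line in the list, a sentence on sources, at most one form item and a small number of death reports. The downside is a modest reporting load and a death count too small for a formal arm comparison. No dose or clinical rule changes.
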